## Abstract

**Background:**

Over 10 million newborns worldwide undergo resuscitation at birth each year. Pediatricians may use electrocardiogram (ECG), pulse oximetry (PO), and stethoscope in determining heart rate (HR), as HR guides the need for and steps of resuscitation. HR must be obtained quickly and accurately. Unfortunately, the current diagnostic modalities are either too slow, obtaining HR in more than a minute, or inaccurate. With time constraints, a reliable robust heart rate detector (HRD) modality is required. This paper discusses a protocol for conducting a methods-based comparison study to determine the HR accuracy of a novel real-time HRD based on 3D-printed dry-electrode single-lead ECG signals for cost-effective and quick HR determination. The HRD’s HR results are compared to either clinical-grade ECG or PO monitors to ensure robustness and accuracy.

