## Introduction

### Background

Each year, over 10 million newborns require resuscitation worldwide, representing more than 10% of all global births [1]. Neonatal resuscitation is the set of interventions at the time of birth to support the establishment of breathing and circulation. These interventions include providing warmth to the infant using a heat source, placing the head in a sniffing posture with neck flexion and upper cervical extension (a position to open the airways), drying the infant, and simulating breathing. Multiple metrics—respiration, infant color, and heart rate (HR)—are measured every 30 seconds to ensure successful neonatal resuscitation [2]. Out of these indicators, HR is identified as the most important for an effective resuscitation process [3]. HR guides decision-making and escalation of care, including positive pressure ventilation, endotracheal intubation, chest compressions, and administration of epinephrine.

Despite the importance of HR in neonatal resuscitation, HR determination is challenging due to a lack of evidence regarding the most rapid and accurate method to assess it. Clinically accepted methods of HR assessment include pulse palpation (umbilical, brachial, and femoral), auscultation with a stethoscope, pulse oximetry (PO) monitoring, and 3-lead electrocardiogram (ECG) monitoring [2]. It is important to note that neonatal resuscitation efforts should be performed within the first minute of life, known as the “golden minute,” to ensure a high success rate and avoid neurodevelopmental disorders and hypoxic injury [4].

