A systematic review compared these different methods in terms of expense, intermittent or continuous HR assessment, and other strengths and weaknesses. Auscultation and pulse palpation are rapid and easily accessible approaches due to their low cost. However, both approaches are highly inaccurate and unreliable, resulting in errors of omission, which causes failure or delay in resuscitation steps and commission through inappropriate intervention [5]. Auscultation requires a pause in resuscitative efforts, which can disrupt the flow of resuscitation and result in a delay in stabilization of the newborn. This method is the most used approach compared to other HR determination approaches, due to its quick and easy accessibility as well as its cost-effectiveness. However, auscultation accuracy is reliant on health care professional experience and can be inconsistent from one practitioner to the other, resulting in inequitable care [6]. On the other hand, PO is relatively inexpensive and noninvasive, and it displays continuous HR and oxygen saturation to the entire team in the delivery room. However, a pulse oximeter can be inaccurate due to motion artifact, ambient light, or poor tissue perfusion, and it takes several minutes to apply and achieve the first data display, potentially delaying resuscitative efforts [4,5].

Current guidelines suggest a 3-lead ECG monitor as the gold standard for HR determination in neonates due to its high speed and accuracy and because of its capabilities to provide continuous visual and auditory data compared to the other modalities, such as PO and auscultation. However, 3-lead ECG has its disadvantages. Errors in the placement of the 3 leads can yield inappropriate ECG signals that cannot be used for HR detection [7]. Additionally, similar to PO, wet electrode ECG placement takes time to apply, surpassing the golden minute of life [5]. ECG adhesive wet electrodes can cause skin damage to premature infants. Moreover, motion artifacts may be present with ECG leads. In rare scenarios, ECG-derived HR may fail to correspond with the effective mechanical contraction of the heart [8]. Most importantly, both PO and 3-lead ECG require additional equipment, which needs to be purchased and maintained, accumulating significant expenses for health care systems [7,8]. Both technologies may not be feasible or accessible in areas with limited health care resources [9].

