### Study Significance and Impact

Given that no single method of HR assessment is clearly superior to others, finding the optimal method to delineate HR within the golden minute after birth remains elusive. Pediatric guidelines recognize this knowledge gap and identify the opportunity to develop new technologies for the rapid, accurate assessment of HR after birth, ideally integrating newborn ECG. Currently, there are no novel medical devices that have been specifically developed to provide rapid and accurate HR immediately after birth. The proposed research study will address several gaps in the scientific study of device development, vital signs measurement and monitoring, and neonatal resuscitation. Recent advances in biomedical sensors and wireless communication technologies have enabled us to develop a novel HRD, targeted to outperform the traditional HR assessment in neonatal resuscitation. The rapid application, measurement, and display of HR on a device located on the neonate addresses significant gaps in the provision of optimal neonatal resuscitation. The HRD is undergoing rigorous design and development, and this study aims to assess its feasibility in quickly detecting accurate HRs in infants using 3D-printed dry electrodes. This early proof-of-concept HRD study will establish the basis for using 3D-printed dry electrodes and determine whether novel HR estimation algorithms are appropriate for neonatal HR applications.

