### Objectives

The overall aim of this research study is to evaluate a novel HRD that may enable timely and appropriate neonatal resuscitation. This study is being completed using a phased sequential user-centered approach. We completed the first phase of this research to determine end-user requirements and preferences for HR assessment in neonatal resuscitation. This phase resulted in the current design and features of the HRD.

The second phase outlines the creation of the HRD conceptual design and proof-of-concept prototype to be used in the final phase of feasibility mentioned in this study.

In the final phase, the focus of this proof-of-concept research study is to examine the functionality, speed, robustness, and reliability of the prototype HRD.

Specific research questions to be answered through this phase are the following:

How long does it take to place the HRD on an infant?Can the prototype HRD detect the HR of newborns?How fast can the prototype detect the HR of newborns?How accurate is the HR detection when compared to PO or ECG?

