#### Data Collection

The displayed HR from the HRD and the PO or ECG monitor will be video recorded for 3 minutes within the same video frame, as shown in Figure 1. Video recording will take place using a dedicated research digital camera mounted on a stand. Video recording will start once the infant is settled and the PO or ECG readings are stable. Stable readings are defined based on the device’s instructions on waiting for an appropriate amount of time after sensor placement for clinical HR determination. The HRD will then be placed on the infant’s chest until a consistent HR is displayed for 3 minutes, at which point video recording will start. After 3 minutes, the HRD will be removed, and then, the recording will be stopped. After the recording is completed, the entire HRD, including electrodes, will be wiped down with a surface disinfectant towelette (CaviWipe; Metrex). HRD device failure will be considered if no HR is displayed on the HRD within 60 seconds of application to the thorax.

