#### Data Management

Video recordings will be individually analyzed by 2 health professional researchers to determine the time it takes to apply the HRD to the thorax and the time from HRD placement to a steady HR display. Each researcher will review and record the HR from the HRD and PO or ECG at 2-second intervals for 3 minutes, providing approximately 90 HR notations per device per patient. For 50 newborns, the total number of HR annotations will be approximately 4500 data points. This will result in multiple HR data points to compare. To avoid human error in the annotation process, discrepancies in the HR of more than 5 beats per minute between the 2 researchers will lead to a reexamination of the video recordings until a consensus can be reached regarding the correct HR. The annotations from the 2 researchers will be averaged for the subsequent analyses.

Additionally, the HRD will record raw ECG signals for the duration of the device being in contact with the infant. Raw ECG data will be collected at 500 Hz sampling rate and transmitted to a research-dedicated laptop. The raw ECG and HR information from the HRD will be stored on different CSV files with a randomized identification number.

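### The HRD's only time limit leaves out placement time, and no planned measure shows how many infants have a heart rate within a minute of starting to apply the device

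*Protocol article*

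**What the plan says.** **Time limit for the HRD.** Methods, Data Collection: "HRD device failure will be considered if no HR is displayed on the HRD within 60 seconds of application to the thorax". No other time limit is set for the device.

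**Times to be taken from the video.** Methods, Data Management: two researchers will "determine the time it takes to apply the HRD to the thorax and the time from HRD placement to a steady HR display". These are two intervals, and the second ends at a steady display. Objectives asks about placement separately ("How long does it take to place the HRD on an infant") and about speed of detection in another question. Study Design lists both as performance measures.

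**How the existing monitors are judged.** The Abstract says that "the current diagnostic modalities are either too slow, obtaining HR in more than a minute, or inaccurate". The Background says of PO that "it takes several minutes to apply and achieve the first data display, potentially delaying resuscitative efforts", and of ECG that "wet electrode ECG placement takes time to apply, surpassing the golden minute of life". It ties the golden minute to birth: "neonatal resuscitation efforts should be performed within the first minute of life". Study Significance and Impact gives the motivation: "finding the optimal method to delineate HR within the golden minute after birth remains elusive".

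**When the video starts.** Data Collection gives two answers. One starts it when the infant is settled and the reference monitor reads stably, which is before the HRD is placed. The other starts it only after the HRD is on the chest and showing a consistent heart rate.

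**The concern.** The article's case for the HRD is speed measured against a one-minute standard. For PO and ECG that standard includes the time to put the sensors on. The HRD's limit omits the matching time, so a low HRD failure rate could be set beside the comparators' times although the clocks start at different points.

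The two timing outcomes do not close this gap. Whether an infant had a heart rate within a minute of starting application depends on the sum of the two intervals in that infant. Separate summaries of each interval do not give it.

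At stake is whether the study can answer its own speed question on the scale used to motivate it. The measured heart rates and the agreement analysis are not affected.

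**Working it through.** **Inputs.** The 60 s limit, counted from application to the thorax (Data Collection). The two separate intervals (Data Management). The planned 50 infants (Recruitment). The article gives no placement or display times, so every such value below is assumed.

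**Where the clock starts.** Application to the thorax could be read as the start of applying. Data Management separates applying the device from the time that runs from placement, which favours chest contact as the start. The rest of the check uses that reading.

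**Timing arithmetic.** Let a be placement time and d the time from chest contact to a displayed heart rate.

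- Failure rule: the device does not fail if d ≤ 60 s.
- One minute with application counted: a + d ≤ 60 s, that is d ≤ 60 − a.
- The two disagree when 60 − a < d ≤ 60. The longest total without a failure is 60 + a.

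| Assumed a (s) | Display limit 60 − a (s) | Longest non-failing total 60 + a (s) |
|---|---|---|
| 5 | 55 | 65 |
| 10 | 50 | 70 |
| 20 | 40 | 80 |
| 30 | 30 | 90 |

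**Why separate summaries are not enough.** Take two invented infants with placement times of 5 and 25 s and display times of 55 and 35 s.

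- Paired as 5 + 55 and 25 + 35, both totals are 60 s and both infants are within the minute.
- Paired as 5 + 35 and 25 + 55, the totals are 40 and 80 s and only one is.
- The means are 15 s and 45 s in both cases, and neither infant is a device failure in either case.

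**Possible size.** Suppose d is lognormal. The expected number of 50 infants without a heart rate by 60 s of total time is 50 × P(d > 60 − a). The column a = 0 is the count under the present failure rule.

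| Assumed median d, log-SD | a = 0 | 5 s | 10 s | 20 s | 30 s |
|---|---|---|---|---|---|
| 15 s, 0.5 | 0.1 | 0.2 | 0.4 | 1.2 | 4.1 |
| 20 s, 0.6 | 1.7 | 2.3 | 3.2 | 6.2 | 12.5 |
| 30 s, 0.6 | 6.2 | 7.8 | 9.9 | 15.8 | 25.0 |

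The gap runs from negligible (fast device, short placement) to large (slow device, long placement). Nothing in the article selects a row or a column.

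**Can the total be computed from the planned data?** Only under the first video start point. Under the second, placement and first display are over before recording begins, so neither interval is on the video.

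**Is the end event the same?** No. The failure rule ends at any displayed heart rate and the timing outcome at a steady one. A total built from the present definitions would end at a different event from the failure rule.

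**The case against.** **The rule is not a golden-minute test.** A reader might infer that the HRD can pass a golden-minute test while missing the minute, or that the failure rate is understated. The documents do not support this. They call the rule a device-failure definition and nowhere call it a speed criterion or call non-failure a success. The infants studied are at least 24 hours old, so the first minute of life is not observed under any clock. This objection stands.

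**Moving the failure clock has a price.** Starting it at pick-up would let operator handling count as device failure. Keeping device response separate from placement is defensible. This stands, and it is why the rule can be left alone.

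**Placement time is already an outcome.** It is, and the sum is simple once both intervals are recorded for each infant. A condensed article may also leave summaries to a fuller document. This lowers the weight of the point but does not remove it: the article itself fixes two intervals with a different end event from the failure rule, and gives a video start under which neither is captured.

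**No head-to-head speed comparison is planned.** True: the reference monitor already reads stably before the HRD is placed, and the remarks on PO and ECG speed are background. But those remarks are the yardstick the article offers, and its speed result will be read against them.

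**The 30-second interval in the Background.** A reader might take it as a second cut-off. It describes how often signs are reassessed during resuscitation, not a limit on the first heart rate, so it gives no ground for one.

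**Conclusion.** The point holds in a limited form. The HRD's only time limit excludes placement, the comparators are criticised with application counted, and no stated measure gives the share of infants with a heart rate within a minute of starting application. The present rule is sound as a technical failure definition.

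The conclusion rests on reading application to the thorax as chest contact. If the start of application was meant, the clock still needs defining. The possible excess over 60 s equals the placement time, 5 to 30 s in the assumed range. How many infants would be affected cannot be stated, because the lognormal figures rest wholly on assumed times. The matter is worth correcting because the change is small and bears directly on one of the four research questions.

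**What to change.** 1. **Data Management:** add, as a main speed measure, the total time within each infant from the start of application to heart rate display. Report the share of all enrolled infants with a heart rate by 60 s of total time, counting device failures as not reached. Keep the two component intervals as descriptions.
2. **Data Collection and Data Management:** choose one display event, first or steady heart rate, and use it in both the failure definition and the timing outcomes. State when the failure clock starts. The 60-second failure rule can otherwise remain.
3. **Data Collection:** reconcile the two video start points so that recording begins before the HRD is placed. Without this, neither interval is captured and item 1 cannot be done.

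**Cost:** slightly longer video for each infant, and a speed figure that may be less favourable than the present failure rate suggests. No extra infants or equipment are needed.

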#### Data Analysis

HR and raw ECG data will be analyzed using MATLAB (the MathWorks). Infant demographics will be analyzed using summary statistics. Continuous variables will be expressed as mean (SD) values, and categorical variables will be expressed as numbers (percentages), unless otherwise stated. The HR from HRD will be compared to PO or ECG using a paired *t* test. The Bland-Altman method will be used to compare the HR derived from each device—the HRD and the PO or ECG monitor, used as reference. The correlation between devices will be assessed using Pearson *r* statistic. Data will be first analyzed using all data points available, and outliers will be defined as 20 beats per minute rate difference between the methods. These discrepancies will be further analyzed to find the likely reason for deviation, including reexamination of the video recordings.

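### HRD failure is defined but enters no named analysis, and one of two conflicting recording-start rules leaves failures unfilmed, so detection ability and speed would rest mainly on infants in whom the device worked

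*Protocol article*

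**What the plan says.** All references are to the protocol article.

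- **Objectives.** Two of the four research questions concern detection and its speed. The first of these is "Can the prototype HRD detect the HR of newborns". Study Design repeats ability to detect and speed of detection as performance measures.
- **Data Collection, failure.** "HRD device failure will be considered if no HR is displayed on the HRD within 60 seconds of application to the thorax".
- **Data Collection, start of recording.** Two rules stand close together. One reads "Video recording will start once the infant is settled and the PO or ECG readings are stable". The other has filming begin only after the HRD reading has settled: "The HRD will then be placed on the infant’s chest until a consistent HR is displayed for 3 minutes, at which point video recording will" (the quote breaks off just before its final verb).
- **Data Management.** Two annotators use the videos "to determine the time it takes to apply the HRD to the thorax and the time from HRD placement to a steady HR display". They also read both devices every 2 seconds for 3 minutes, giving about 90 readings per device per infant and about 4500 over 50 infants.
- **Data Analysis.** "Continuous variables will be expressed as mean (SD) values", with numbers and percentages for categorical variables, unless stated otherwise. HRD and reference are compared by paired t test, Bland-Altman and Pearson r. "Data will be first analyzed using all data points available", and the same sentence goes on to define outliers as a 20 beats per minute difference.

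**The concern.** Whether a device can detect heart rate is a question about every infant to whom it was applied. The failure definition supplies the event, but no named analysis uses it and no denominator is given. The three comparison methods work on pairs, so an infant without an HRD value, or a blank 2-second reading, drops out without trace. Speed has the same problem: a mean cannot take in an infant who never reaches the endpoint, so the slowest results are the ones lost.

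The recording rules could build this selection into the data. If filming waits for a consistent HRD display, failed infants have no video, and no later analysis plan can recover their video-based times. There is also a gap between definitions. Failure concerns any display by 60 s, while the timed endpoint is a steady display. An infant with a brief number and no steady reading is not a failure, and under the second start rule is not filmed.

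At stake is a device that fails or drops out often yet is reported as fast and accurate.

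**Working it through.** **1. The plan's own count.** Inputs from Data Management: 3 minutes, 2-second intervals, 50 infants. 180 / 2 = 90 readings per device per infant, and 50 × 90 = 4500 pairs. The stated figure reproduces, but only if no infant fails and no reading is blank. Each failed infant removes 90 / 4500 = 2% of the pairs and leaves the bias, limits of agreement and r of the remaining infants unchanged.

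**2. The two start rules side by side.**

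| | Start when reference is stable | Start when HRD display is consistent |
|---|---|---|
| HRD placement on video | yes | no |
| Application time readable from video | yes | no |
| Time to steady display readable from video | yes | no |
| Failed infant filmed | yes | no |

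Only the first rule is compatible with the times that Data Management takes from the video.

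**3. Detection with all infants in the denominator.** The article gives no expected failure rate, so the counts below are assumptions. Exact (Clopper-Pearson) 95% intervals, n = 50 applied, pairs left = 90 × (50 − failures):

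| Failures | Detected within 60 s | 95% CI | Pairs left |
|---|---|---|---|
| 0 | 100% | 92.9-100% | 4500 |
| 1 | 98% | 89.4-99.9% | 4410 |
| 3 | 94% | 83.5-98.7% | 4230 |
| 5 | 90% | 78.2-96.7% | 4050 |
| 10 | 80% | 66.3-90.0% | 3600 |

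Even with no failure, the data would be compatible with a failure rate of up to 7.1%.

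**4. Mean time in detected infants only.** Let f be the proportion undetected at 60 s and C = E[T | T ≤ 60]. The comparator is the 60 s restricted mean, in which undetected infants count as 60 s: R = (1 − f)C + 60f. The understatement is 1 − C/R.

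*Exponential times (assumed).* Rate λ = −ln(f)/60, C = [1/λ − f(60 + 1/λ)]/(1 − f), R = (1 − f)/λ.

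| f | C (s) | R (s) | Understatement | Median, all infants (s) |
|---|---|---|---|---|
| 2% | 14.1 | 15.0 | 6% | 10.6 |
| 5% | 16.9 | 19.0 | 11% | 13.9 |
| 10% | 19.4 | 23.5 | 17% | 18.1 |
| 20% | 22.3 | 29.8 | 25% | 25.8 |

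*Lognormal times (assumed), log-SD σ = 0.8, μ = ln(median).* f = 1 − Φ[(ln 60 − μ)/σ], C = exp(μ + σ²/2) Φ[(ln 60 − μ − σ²)/σ]/(1 − f).

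| Median (s) | f | C (s) | R (s) | Understatement |
|---|---|---|---|---|
| 20 | 8% | 21.6 | 24.8 | 13% |
| 30 | 19% | 27.0 | 33.3 | 19% |
| 40 | 31% | 30.5 | 39.6 | 23% |

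Example, median 30 s: (ln 60 − ln 30)/0.8 = 0.866, so f = 0.193. R = 0.807 × 27.0 + 60 × 0.193 = 33.3 s, and 1 − 27.0/33.3 = 19%.

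In every scenario fewer than half the infants are undetected, so the median over all infants stays estimable.

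**The case against.** The strongest reply is that this is silence in a condensed article, not a stated exclusion. Much of that stands.

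- A reader might infer that failures drop out of every stated analysis. No passage excludes them. Failure is a yes/no variable that the numbers-and-percentages rule could report over all infants, and the F1-score in the Abstract, which is not defined, might count non-display as a miss.
- A reader might infer that times are censored at 60 s. The article does not say observation stops there. Sixty seconds is the cut-off for any display, a steady display may come later, and Study Procedures has the HRD held on the thorax for 3 minutes.
- The mean (SD) sentence follows the one on infant demographics and allows exceptions. Applying it to detection times is a fair reading, but not an explicit one.
- The sentence on using all available data points most naturally means that outliers stay in the first analysis. It is not a missing-data rule.
- Infants whose device never settles are not lost altogether. The other start rule would film them, and the HRD's raw ECG and heart rate are stored separately from the video.
- Comparing the detected-only mean with the unrestricted mean would give a shortfall of about 22-45% in the lognormal scenarios. That is too harsh a yardstick, because the unrestricted mean depends on the assumed tail beyond 60 s.

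What the reply does not remove: the three comparison methods need a displayed HRD value, failure is linked to no named analysis, and the start rules contradict each other. A fuller plan could supply a denominator and a time summary. It could not recover video-based times from infants who were never filmed.

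**Conclusion.** The point holds in a limited form. Followed literally, the article would answer its detection and speed questions mainly from infants in whom the device worked, because failure has no analysis or denominator, the comparison methods condition on a displayed value, and one start rule films only after a consistent display. The text does not support saying that failures are excluded by design or that times are censored at 60 s.

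The direction of the bias in a detected-only mean is clear: it flatters the device whenever any infant is undetected. Its size cannot be had from the article. It is about 6-25% below the 60 s restricted mean for exponential times with 2-20% undetected, and about 13-23% below for lognormal times with log-SD 0.8 and medians of 20-40 s. Both rest on assumed distributions and failure rates, and both treat infants undetected at 60 s as left out of the mean. The change is worth making and is cheap. The conflict between the start rules is the part to settle first, since it affects what is collected.

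**What to change.** 1. Reconcile the two start rules in Data Collection so that recording begins before HRD placement for every infant.
2. Report detection within 60 s as a number over all infants in whom the HRD was applied, with an exact 95% CI.
3. Summarise time to first display and time to steady display by Kaplan-Meier median and quartiles, in place of mean (SD). Retain infants who never reach the endpoint and censor them when their own observation ends, not automatically at 60 s. An infant with a display but no steady reading then counts as detected for the first endpoint and as not reaching the second.
4. Beside the limits of agreement, give the percentage of scheduled 2-second readings with an HRD value. A combined score of displayed and within tolerance is an optional extra, and would need a tolerance that the article does not give.

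The cost is a little more filming and annotation, including logging of blank readings. The speed and reliability figures may come out less favourable.
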